## Abstract

**Background:**

Age-related cognitive decline (ARCD) is of major societal concern in an ageing population, with the development of dietary supplements providing a promising avenue for amelioration of associated deficits. Despite initial interest in the use of phospholipids (PLs) for ARCD, in recent years there has been a hiatus in such research. Because of safety concerns regarding PLs derived from bovine cortex, and the equivocal efficacy of soybean-derived PLs, there is an important need for the development of new PL alternatives. Phospholipids derived from milk proteins represent one potential candidate treatment.

**Methods:**

In order to reduce the effects of age-associated memory impairment (AAMI) the Phospholipid Intervention for Cognitive Ageing Reversal (PLICAR) was developed to test the efficacy of a milk protein concentrate rich in natural, non-synthetic milk phospholipids (Lacprodan® PL-20). PLICAR is a randomized, double-blind, placebo-controlled parallel-groups study where 150 (N = 50/group) AAMI participants aged > 55 years will be randomized to receive a daily supplement of Lacprodan® PL-20 or one of two placebos (phospholipid-free milk protein concentrate or inert rice starch) over a 6-month (180-day) period. Participants will undergo testing at baseline, 90 days and 180 days. The primary outcome is a composite memory score from the Rey Auditory Verbal Learning Test. Secondary outcomes include cognitive (verbal learning, working memory, prospective and retrospective memory, processing speed and attention), mood (depression, anxiety, stress and visual analogue scales), cardiovascular (blood pressure, blood velocity and pulse wave pressure), gastrointestinal microbiota and biochemical measures (oxidative stress, inflammation, B vitamins and Homocysteine, glucoregulation and serum choline). Allelic differences in the Apolipoprotein E and (APOE) and *Methylenetetrahydrofolate reductase* (MTHFR) gene will be included for subgroup analysis. A subset (N = 60; 20/group)) will undergo neuroimaging using functional magnetic resonance imaging (fMRI) and magnetoencephalography (MEG) in order to further explore *in vivo* central mechanisms of action of Lacprodan® PL-20. This study will enable evaluation of the efficacy of milk-derived phospholipids for AAMI, and their mechanisms of action.

**Trial Registration:**

The trial is jointly funded by Arla Foods and Swinburne University of Technology, currently recruiting and is registered on the Australian New Zealand Clinical Trials Registry as ACTRN12613000347763.

## Background

Cognitive deficits including learning and memory impairment are one of the most prominent and debilitating consequences of normal and pathological ageing in humans. A consistent finding in research on ageing and cognition is that performance across various tests of memory is lower with increased age. Meta-analyses of cross-sectional and longitudinal datasets have demonstrated approximately 40 to 60% decline in cognitive speed at age 80 compared to age 20 years in non-demented adults [1]. These cognitive deficits are of considerable concern to elderly individuals, with up to 50% of adults aged 64 years or older reporting difficulties with their memory [2]. There is an increasing awareness of the possibility that dietary modification can alter the course of age-related cognitive decline.

Frequent dairy food intake is associated with better cognitive function, although the exact underlying mechanisms are yet to be determined. The positive correlation between increased dairy intake and cognitive function seems partly to be a result of counteracting metabolic syndrome, by reducing cardiovascular (CV) risk factors such as type 2 diabetes, hypertension, obesity and hyperlipedimia [3-5]. In a recent paper by Crichton *et al*. [6], the authors support this link and in addition argue that apart from counteracting the CV risk factors, dairy consumption provides additional benefits in relation to cognitive function (for example, after adjusting for CV disease, lifestyle and dietary factors). Recent advances in dairy manufacturing, which enable the enrichment of phospholipid components in milk also offer a promising new avenue for the treatment of age-related cognitive decline.

### Phospholipids and the amelioration of cognitive decline

Bovine milk contains a vast range of phospholipids and complex lipids, with important biological functions. Phospholipids are substances with both a hydrophilic (water-liking) head and hydrophobic (water-repellent) tail segment which are major building blocks for cellular membranes, including neuronal cells, where they arrange themselves into lipid bilayers [7]. Relevant phospholipids in relation to cognitive performance include phosphatidylserine (PS) and phosphatidylcholine (PC) as well as the related substances sphingomyelin and the sialic-acid-containing gangliosides. Pharmacokinetic studies of PS have revealed good bioavailability when consumed orally. Following ingestion, the headgroup is absorbed intact through the intestinal wall into the bloodstream, while the fatty-acid tail segments at position 2 are often removed and later re-added. After crossing the blood–brain barrier the fatty acid at position 2 is typically occupied by either oleic (C18:1) or docosahexaenoic acid (DHA, C22:6) in the brain [8,9].

#### Phosphatidylserine (PS)

PS is a naturally occurring membrane phospholipid that is found in high concentrations in brain tissue, where it comprises 10 to 20% of the total phospholipid pool [10]. PS plays an important role in a host of cellular functions including mitochondrial membrane integrity, presynaptic neurotransmitter release, postsynaptic receptor activity and activation of protein kinase C in memory formation [7,11]. PS enhances the activities of membrane-bound enzymes involved in signal transduction [12] and plays a key role in the biosynthesis and release of several neurotransmitters, including acetylcholine [13,14], norepinephrine [15], serotonin and dopamine [16]. PS has also been found to elevate glucose metabolism [17].

In relation to the cholinergic system, PS has been found to restore age-related decreases in choline-acetyltransferase-positive neurons [18] as well as densities of muscarinic and N-methyl-D-aspartate (NMDA) receptors [19,20]. Increases in nerve growth factor (NGF)-receptor density have been reported in aged animals following PS supplementation, as well as increases in neuronal numbers and size [21]. Other beneficial effects of PS supplementation include protection from cell death [22] due to increased membrane fluidity [23] as well as anti-inflammatory and antioxidant effects [24]. Behavioural animal experiments using PS have provided evidence of improvements in spatial memory [25], retention of passive avoidance [15], exploration and memory retrieval [26] as well as improvement of avoidance performance [27]. Prevention of scopolamine-induced learning deficits have also been reported [28-31], together with an attenuation of memory deficits associated with reserpine-induced catecholamine depletion [32].

PS is the most studied of the phospholipids in regards to human clinical trials of dementia and cognitive decline. Five double-blind randomized trials have been conducted using PS in Alzheimer’s disease (AD) [33-37]. Clinical global impressions of change and activities of daily living were found to be improved with daily doses of 200 to 300 mg up to six months. In milder cases of AD, significant improvements to concentration, learning and memory for names, locations and recent events were also observed [7,11]. In the largest of these studies involving 494 elderly patients with moderate to severe cognitive decline, Cenacchi *et al*. [37] reported improvements to memory and learning following 300 mg PS/day for 6 months.

In elderly populations with mild cognitive impairment and age-associated memory impairment (AAMI), PS has also been found to be effective in ameliorating cognitive declines. Crook *et al*. [38] administered 300 mg/day PS to 149 elderly patients (aged 50 to 75 years) with age-associated memory impairment for 12 weeks, and observed significant improvements in performance tests of learning and recall abilities such as name-face matching. In a multi-centre trial by Villardita *et al*. [39], 300 mg/day PS versus placebo was administered to 170 elderly patients for 90 days. Significant improvements in attention, concentration and short-term memory were found in those receiving PS. These earlier trials were conducted using PS derived from bovine cortex, but more recently trials have also been conducted using soybean (SB)-derived PS due to concerns over bovine spongiform encephalopathy. The results in relation to SB-PS have been more mixed, with Jorissen *et al*. [40] reporting no significant effects on learning and memory, whereas more recently Vakhaporva *et al*. [41] and Kato-Kataoka *et al*. [42] reported significant improvements to verbal learning following ≥3 months supplementation. An intriguing study by Hellhammer *et al*. [43] using the same milk-derived phospholipids as the current study (PL-20) also reported improvements to working memory function following 3 weeks supplementation in healthy adults aged 30 to 55 years.

#### Phosphatidylcholine (PC)

Choline is an essential nutrient critically needed for synthesis of the neurotransmitter acetylcholine; important in brain functions, such as memory and mood, but also important in skeletal-muscle control, heart rate and breathing. Numerous animal studies demonstrate that choline is necessary for normal development of the memory function and sub-optimal dietary intake of choline by the pregnant mother and later by the infant and child directly affects brain development and results in permanent changes in brain function (Zeisel *et al*. 1991). Choline or its metabolites, are also needed for the structural integrity and signaling functions of cell membranes; it is the major source of methyl-groups in the diet (one of choline’s metabolites, betaine, participates in the methylation of homocysteine (HCy) to form methionine), and it directly affects cholinergic neurotransmission, transmembrane signaling and lipid transport/metabolism [44,45]. Nagata *et al*. [46] documented recently that dietary supplements of PhosChol compounds (1,2-dilinoleoyl-sn-glycero-3-phosphocholine; DL-PC and 1-palmitoyl-2-oleoyl-sn-glycero-3-phosphocholine; PO-PC) ) enhanced the memory and learning ability in the elderly in the Mini Mental State Examination (MMSE). In another placebo-controlled clinical trial, Ladd *et al*. [47] found that the supplementation of SB-PC in normal college students lead to an improvement in explicit memory function due to increased choline supply and improved cholinergic function.

A poor folate status is associated with cognitive decline and dementia in older adults [48]. Although impaired brain methylation activity and HCy toxicity are widely thought to account for this association, how folate deficiency impairs cognition is still uncertain. Troen *et al*. [49] found a correspondence of cognitive outcomes to changes in brain membrane PC content (in rats), which suggests that altered PC and possibly choline metabolism might contribute to the manifestation of folate deficiency-related cognitive dysfunction. Up to 50% of older people have been reported to have folate deficiency, with higher levels in those institutionalized [50]. For this reason, there is a sound theoretical reasoning to speculate on a positive beneficial outcome in relation to cognition and boosting memory with choline and choline-containing compounds [44].

Elevated total homocysteine (tHcy), a risk factor for many chronic diseases including cognitive decline, can be remethylated to methionine by folate [51]. Alternatively, tHcy can be metabolized by other 1-carbon nutrients, that is, betaine and its precursor, choline. Elias *et al*. [48] reported that tHcy levels are inversely associated with visual-spatial organization, working memory, scanning-tracking, and abstract reasoning. Chiuve *et al*. [52] assessed the association between the dietary intakes of betaine and choline and the concentration of tHcy. They found the total choline + betaine intake to be inversely associated with tHcy. In a double-blind, placebo-controlled clinical trial Olthof *et al*. [53] investigated the supplementation with soybean PC (PhosChol) on homocysteine plasma concentrations in men with mildly elevated levels. They found that PC was able to reduce homocysteine levels, thus supporting the link between dietary intake of PC and homocysteine plasma levels.

#### Gangliosides

Brain content of specific gangliosides (for example, GM1) has been documented to decrease with age, and a low GM1 content has been observed in the brains of patients with AD [54]. Exogenously administered gangliosides have been shown to exhibit neurotrophic action, and to increase the release of brain-derived neurotrophic factor (BDNF) *in vitro*[55]. Experimental data have shown that gangliosides, and in particular, GM1, exhibit properties similar to the neurotrophins. The neurotrophins promote neurogenesis, which is essential for specific cognitive functions that decline in some neurological disorders and in ageing [56]. A systemic administration of GM1 in rats ameliorated the age-related decreased activity of choline acetyl transferase and choline uptake in the brain of aged rats as well as improved spatial learning and memory tasks in the aged rats [57]. Dietary gangliosides increase total brain-ganglioside content in rats [58].

#### Sphingomyelin (SM)

The myelin content of the brain decreases with age and the age-related slowing in cognitive processing speed is associated with myelin integrity in a very healthy elderly population [59]. Dietary bovine SM contributes to central nervous system (CNS) myelination [60]. Sphingomyelin is also a source of choline. Clinical trials are yet to be conducted in order to assess the *in vivo* neurocognitive effects of SM in humans.

### Methods/Design

Phospholipid intervention for cognitive ageing reversal (PLICAR) is a randomized, double-blind, placebo-controlled, three-arm, stratified parallel-groups clinical trial with participants randomized to receive a minimum daily dosage of 2.7 g phospholipids (and minimum daily dose of 300 mg/day PS) from Lacprodan® PL-20 or one of two placebos (milk protein concentration or rice starch) over a 180-day (6-month) period. The maximum daily dose of Lacprodan® PL-20 will be 16 g/day. Participants will be stratified according to age, IQ using Raven’s Progressive Matrices (RPM) [61] and baseline score on the Wechlser Memory Scale-Revised (WMS-R) [62].

### Aims and study hypotheses

The primary objective of the current study is to evaluate the chronic effects of daily Lacprodan® PL-20 supplementation on cognitive performance in a healthy elderly population with age-associated memory impairment (AAMI). The secondary objectives of the study are to investigate mood and CV effects of Lacprodan® PL-20 as well as the *in vivo* mechanisms of action by which Lacprodan® PL-20 may improve cognitive function. To this end, a range of measurement modalities will be employed including assessments of CV function, blood biomarkers, gastrointestinal (GI) microbiota, pharmacogenomics and brain activity assessed by functional magnetic resonance imaging (fMRI), magnetoencephalography (MEG) and diffusion tensor imaging (DTI).

Performance on the various outcome measures for participants receiving Lacprodan® PL-20 will be compared to the performance of participants receiving (i) an inert placebo powder made of rice starch, and (ii) a milk-protein concentrate without phospholipids that has been matched for protein content and total calories. The reason/rationale for including two comparator treatments (rather than one) is the opportunity to address separate research questions. The first comparison (to inert placebo) addresses the research question of whether Lacprodan® PL-20 as a whole has benefits for cognitive function and other secondary outcomes. The second comparison to a milk-protein concentrate without phospholipids addresses a more specific research question regarding whether benefits to cognition and other outcomes associated with Lacprodan® PL-20 can be attributed specifically to the phospholipid content in the formula. In consideration of previous research demonstrating cognitive benefits associated with dairy components other than phospholipids [3], the inclusion of a third treatment arm was deemed necessary in order to properly delineate the effects of phospholipids versus other dairy components present in Lacprodan® PL-20.

On the basis of previous human clinical studies with bovine and plant-derived phospholipids, it is hypothesised that in comparison to the inert placebo, Lacprodan® PL-20 supplementation over 180 days will result in significant improvements on our primary variable, namely a composite memory score computed from the Rey’s Verbal Learning Test (RVLT). We are also exploring the possibly that the treatment may benefit other elements of cognitive performance (including processing speed and global functioning). A second hypothesis is that cognitive benefits of a lesser magnitude will be observed when comparing supplementation with Lacprodan® PL-20 with milk protein concentrate (MPC) without phospholipids placebo over 180 days. Additionally we are exploring the effects of Lacprodan® PL-20 on a number of central, CV and GI biomarkers.

### Study site

PLICAR will be conducted at the Centre for Human Psychopharmacology, Swinburne University of Technology, Melbourne, Australia.

### Participants

A total of 150 healthy elderly participants (≥55 years) with AAMI will take part in the study. AAMI is defined on the basis of criteria first outlined by Crook *et al*. [63,64]: (i) a score >25 on the Memory Complaint Questionnaire (MAC-Q [64]) and (ii) a score ≤1 standard deviation below the mean for healthy young adults on the paired associates test from the WMS-R [62]. Participants will be excluded from participation if they are currently diagnosed with dementia and/or score <24 on the MMSE [65]; have a neurological, cardiac, endocrine, GI or bleeding disorder; have a psychiatric illness, including moderate-to-severe depression, as defined as a score ≥20 on the Beck Depression Inventory II (BDI-II) [66]; have a current or previous history of alcoholism and/or substance abuse; have a known or suspected allergy to cow’s milk and/or lactose intolerance; are a current smoker, or are not fluent in the English language. To be eligible, participants also cannot be currently taking any medications or herbal/dietary supplements with known cognitive effects. The study is jointly funded by Arla Foods (Denmark) and Swinburne University of Technology. It was ethically approved by the Swinburne University Human Research Ethics Committee (project number 2012/294) and all participants will provide written informed consent. The trial has been registered with the Australian and New Zealand Clinical Trials Registry (ACTRN12613000347763).

### Procedure

Eligible participants are required to attend four testing sessions. An overview of the testing sessions is provided in the clinical trial flow chart (Figure 1).

**Figure 1 F1:**
[figure not shown]
**Phospholipid intervention for cognitive ageing reversal (PLICAR) protocol flow diagram.** AAMI, age-associated memory impairment; MAC-Q, Memory Complaint Questionnaire; MMSE, Mini Mental State Examination; BDI-II, Beck Depression Inventory II; BMI, body mass index; RPM, Raven’s Progressive Matrices; APOE, Apoliprotein E; MTHFR, Methylenetetrahydrofolate reductase; MRI, magnetic resonance imaging; MEG, magnetoencephalography; MPC, milk protein concentrate; TICS-M telephone interview for cognitive status modified.

#### Visit 1 (screening/practice)

During the first visit, voluntary written informed consent is obtained from all participants. Then the participants are further screened for eligibility and administered the MMSE, MAC-Q, WMS-R and BDI-II. A detailed medical history is also taken, a dietary questionnaire is administered [67,68] and demographic information is collected, which includes body mass index (BMI), age, educational background and general intelligence (as measured by RPM). All eligible participants are then required to complete practice versions of all the cognitive outcome measures to be used in the study.

#### Visit 2 (Baseline)

The second visit will be scheduled for one week following the screening/practice visit. In preparation for the baseline visit, all participants will be required to collect and store their faecal sample (as per the procedure provided in the faecal sample collection kit) a day before the actual visit. The faecal sample for GI microbiota analysis will be deposited at the Centre for Human Psychopharmacology, Swinburne University, when the participant comes for the baseline visit. The faecal samples will be stored at -80°C until further analysis. Also in preparation, participants will be required to fast from 10 pm the night before. A fasting blood sample will then be taken in order to assess the baseline biochemical measures, together with a separate blood sample, which will be used for Apolipoprotein E (APOE) and *Methylenetetrahydrofolate reductas*e (*MTHFR*) genotyping. Following the blood samples, participants will eat a light breakfast. Half an hour after breakfast, participants will be required to complete all pre-dose cognitive, mood and CV measures. Participants will then be randomized to their treatment group (Lacprodan PL-20® or MPC or rice starch) and consume their first sachet of study treatment dissolved in water. A lunch break of 90 minutes will then follow, before post dose testing on all cognitive, mood and cardiovascular measures. At the conclusion of the baseline study visit, participants will be provided with enough study treatment for the next 90 days.

#### Visits 3 and 4 (90 and 180 days)

The schedule of events for the 90-day and 180-day visits is identical to that for the baseline visit. On the day of each study visit participants will be required to wait until the completion of pre-dose assessments before consuming their daily study treatment.

#### Neuroimaging sub-study

Participants involved in the neuroimaging sub-study will be required to attend two additional sessions, the first in the week preceding their baseline visit and the second in the week preceding their 180-day visit (see Figure 1). In the second visit they will be required to consume their study treatment as usual in the morning before the scans. This is due to the fact that the neuroimaging sub-study is only concerned with the chronic effects of PL-20 on brain function.

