### Secondary outcomes

A range of secondary outcomes will be used, encompassing cognitive performance, mood, CV, GI microbiota, biochemical, genetic and brain imaging modalities. Secondary outcomes will include other elements of cognitive performance as measured by a battery of well-validated and highly sensitive cognitive tests. Traditional paper-and-pencil neuropsychological tests as well as computerized tasks have been included. These tests will be implemented at baseline, 90 days and 180 days (pre-dose) in order to capture chronic effects. This battery will consist of the MMSE [65], the Prospective and Retrospective Memory Questionnaire (PRMQ) [73], RVLT [69,70], Spatial Working memory and Contextual Memory tasks from the Swinburne University Computerized Cognitive Ageing Battery (SUCCAB [74]), rapid visual information processing (RVIP), serial 3 s and 7 s subtraction and the Hick’s reaction time paradigm. In order to capture potential acute cognitive effects associated with Lacprodan® PL-20 supplementation, the SUCCAB tests, RVIP, serial 3 s and 7 s subtraction and Hick’s reaction time will also be administered 90 minutes post dose.

The MMSE [65] is a global measure of cognitive function that has been used extensively both as a diagnostic tool for dementia screening as well as a cognitive outcome measure for gauging the efficacy of chronic nutraceutical interventions in elderly participants, for example [71,75,76]. The MMSE was included in the current study due to its widespread use in previous research; however problems with ceiling effects and insensitivity to change amongst high-functioning individuals have been previously well-documented [77].

The PRMQ [73] is a self-report instrument which provides a measure of retrospective as well as prospective memory slips in everyday life. The PRMQ was included in the current study in order to provide an ecologically valid measure of typical memory complaints that may be of concern to elderly individuals. Although most memory complaint questionnaires focus exclusively on failures to remember previous information (retrospective memory), the PRMQ is unique in that it additionally provides a measure of prospective memory failures, which are failures relating to tasks that need to be completed at a certain time (for example, remembering to turn up to an appointment on time) [73,78].

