#### Cardiovascular assessment

There is evidence to suggest that increases in arterial stiffness with ageing, which are reflected in measures of blood flow velocity, may be a contributing factor in cognitive decline [95,96]. Previous research suggests that milk proteins may increase insulin secretion, as well as help to reduce blood pressure and plasma cholesterol levels [3,97]. Further, high levels of B12 present in milk may also help to lower HCy levels, which are a contributing factor to CV disease [98]. In light of the fact that Lacprodan® PL-20 is an MPC, it could be argued that chronic supplementation may have a positive influence on CV function. By this reasoning, the inclusion of CV parameters in the current study will enable exploration of whether improvements to CV function are a mechanism by which with Lacprodan® PL-20 may achieve cognitive benefits.

CV function will be assessed using brachial blood pressure, aortic blood pressure, carotid-femoral pulse wave velocity (PWV) as well as blood flow velocity in the medial carotid artery and the common carotid artery (CCA). Brachial blood pressure will be calculated with the participant seated and following a five-minute rest period using a clinically validated automated sphygmomanometer. Aortic blood pressure, pulse pressure and PWV (all aspects of arterial stiffness and CV pressures) will be measured non-invasively using the SphygmoCor device. Applanation tonometry of the radial artery will be used to estimate aortic pressures and wave reflections, and applanation of the carotid and femoral arteries will be used to measure PWV. A non-invasive transcranial Doppler system will be used to record middle cerebral artery (MCA) blood velocity by placing a sensor close to the participant’s ear and common carotid artery (CCA) blood velocity will be recorded by placing a hand-held sensor at the base of the participant’s neck. All CV measures will be assessed pre- and post dose at the baseline, 90-day and 180-day study visits in order to capture both acute and chronic effects associated with Lacprodan® PL-20 supplementation.

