#### Neuroimaging

Neuroimaging with fMRI and MEG will be conducted in a subset of 60 participants in order to further explore the *in vivo* mechanisms of action of Lacprodan® PL-20 in the brain. Previous neuroimaging studies using PS supplementation in AD have been conducted using electroencephalography (EEG) as well as positron emission tomography (PET) [133-135]. PET results revealed that for the PS group there was increased glucose metabolism during a visual recognition task across a number of brain regions, most notably the temperoparietal regions [133]. However, to date no further neuroimaging studies have been conducted using phospholipid interventions, and to the best of our knowledge none have been conducted using MRI or MEG.

In the current study structural and functional MRI scans will be acquired using a Siemens 3 Tesla Tim Trio MRI scanner (Erlangen, Germany), located at the Centre for Human Psychopharmacology, Swinburne University of Technology. During the initial scan, a structural image will be obtained for each participant and used as a reference point for further functional scans. Scanning for DTI analysis, a measure of white matter integrity, will also be conducted. Following DTI there will be scanning in a resting state in order to assess activity in the default mode network (DMN) for approximately 6 minutes. Additional analysis of cell membrane fluidity will also be conducted by using the T2 signal timing information (relaxometry) while in a resting state. Changes in the blood oxygenation-level dependent (BOLD) signal will also be analysed while participants complete in-scanner versions of verbal episodic memory (approximately 20 minutes) and N-Back working memory tasks (approximately 20 minutes).

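### Imaging participants take the product before the follow-up scan, so the functional imaging contrasts cannot be attributed to chronic effects alone

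*Protocol article*

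**What the plan says.** The Neuroimaging sub-study section places one scan in the week before the baseline visit and one in the week before the 180-day visit. For the later session it states: "In the second visit they will be required to consume their study treatment as usual in the morning before the scans". It justifies this by saying that "the neuroimaging sub-study is only concerned with the chronic effects of PL-20 on brain function".

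The main study handles dosing differently:

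- Visits 3 and 4: on each visit day "participants will be required to wait until the completion of pre-dose assessments before consuming their daily study treatment".
- Secondary outcomes, cognitive battery: "These tests will be implemented at baseline, 90 days and 180 days (pre-dose) in order to capture chronic effects". Some computerized and serial-subtraction tests are repeated 90 minutes after dosing, with the purpose given as "In order to capture potential acute cognitive effects associated with Lacprodan® PL-20 supplementation".
- Mood: chronic change is measured before the dose, and the Bond-Lader scales are repeated after it to look for acute effects.
- Cardiovascular assessment: all measures are "assessed pre- and post dose at the baseline, 90-day and 180-day study visits in order to capture both acute and chronic effects". These include cerebral blood flow: "A non-invasive transcranial Doppler system will be used to record middle cerebral artery (MCA) blood velocity".

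Among the imaging endpoints, the Neuroimaging section states: "Changes in the blood oxygenation-level dependent (BOLD) signal will also be analysed while participants complete in-scanner versions of verbal episodic memory". The Analysis section compares PL-20 with the milk protein and inert placebo arms in predefined brain regions.

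**The concern.** The stated reason points to the opposite instruction. If only chronic effects are of interest, the article's own convention is to assess before that day's dose. Dosing first lets any acute effect into the measurement.

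Randomization does not remove such an effect. Each arm takes its own product that morning, and under Treatments the products differ: up to 16 g PL-20, 12 g phospholipid-free milk protein concentrate, or 20 g rice starch. Only same-day effects common to all arms cancel. A between-arm difference in BOLD, resting-state or MEG change could therefore include a same-day component and still be reported as a chronic mechanism of PL-20. Demonstrating mechanism is the purpose of the sub-study.

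**Working it through.** **Dosing state at each scan**

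| Scan | Timing | Prior exposure | Same-day dose |
|---|---|---|---|
| 1 | Week before the baseline visit | None (first sachet is taken at the baseline visit, after randomization) | No |
| 2 | Week before the 180-day visit | About six months | Yes, before scanning |

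Write C for the between-arm chronic effect and A for the between-arm effect of that morning's dose. Then:

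- Difference in change, as planned (dosed at scan 2): C + A.
- Difference in change if the sachet followed the scan: C, with the last dose about a day earlier.

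Neither the text nor Table 2 describes a second follow-up scan in the undosed state, so the imaging data alone cannot estimate A.

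**Does the article treat A as possible?** Yes. It adds post-dose cognitive, mood and cardiovascular measurements to look for acute effects. Middle cerebral artery velocity is measured both before and after dosing, and the fMRI tasks depend on a blood-oxygenation signal. The step from velocity to BOLD is my inference; the article does not make it, and it does not extend to MEG.

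**Illustration of size.** The article gives no value for A, so the values of d below are assumptions. Suppose C = 0 and A = d standard deviations of change. Take one pairwise regional comparison by two-sample t test, two-sided:

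- degrees of freedom = 2n − 2
- noncentrality = d × √(n/2)
- rejection probability from the noncentral t distribution

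At n = 20 per arm, df = 38, the critical value at 0.05 is 2.024, and √(20/2) = 3.162. The noncentrality is 0.632, 1.581 and 2.530 for d = 0.2, 0.5 and 0.8. With the 20% drop-out from the Sample size section, n = 20 × 0.8 = 16, df = 30 and √(16/2) = 2.828.

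| Per arm | Alpha | d = 0.2 | d = 0.5 | d = 0.8 |
|---|---|---|---|---|
| 20 | 0.05 | 9.5% | 33.8% | 69.3% |
| 16 | 0.05 | 8.5% | 27.8% | 59.1% |
| 20 | 0.01 | 2.5% | 14.4% | 43.8% |
| 20 | 0.005 | 1.4% | 9.6% | 34.2% |

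The last two rows allow for the Analysis section's statement that significance is corrected for multiple comparisons. The method is not given, so 0.01 (about five regions under Bonferroni, 0.05/5) and 0.005 (about ten, 0.05/10) are assumed. Each rate should be read against its own nominal alpha. At d = 0.5 and 20 per arm, the rate is roughly 7 times nominal at 0.05 (33.8/5), 14 times at 0.01 (14.4/1) and 19 times at 0.005 (9.6/0.5).

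**The case against.** The strongest defence is that participants are scanned once, in their ordinary on-treatment state. The product is normally taken with breakfast, the instruction says as usual, and the rationale may only be explaining why the imaging session lacks the before-and-after structure of the main visits. Scanning in the on-treatment state is a legitimate target. It is, however, acute plus chronic, and the article says chronic only, so the dosing or the claim has to change.

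Other points carry some weight:

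- No same-day effect of PL-20 is demonstrated. The article speaks only of potential acute effects, and the earlier PL-20 findings it cites are not presented as single-dose effects. This makes the problem one of attribution, not a proven bias.
- The milk protein comparator is matched for protein and total calories, so same-day effects of those should largely cancel in that contrast. An acute phospholipid effect would not cancel, and the rice starch contrast lacks the same protection.
- The percentages are generic power figures for assumed effects, and correction for multiplicity lowers them. They illustrate what could happen and do not support the finding, which rests on the dosing instruction and its stated reason.
- Recruitment is under way, and changing dosing partway through would mix states within small groups. This bears on which remedy to choose.

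**Conclusion.** The concern holds. The instruction to dose before the follow-up scan contradicts the reason given for it, and the functional imaging contrast estimates a combined chronic and same-day effect.

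The reach is limited to task BOLD, resting-state and MEG measures in up to 60 participants, 20 per arm. Structural MRI and DTI are less exposed to a single dose. The primary outcome and its analysis are not affected.

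The size of the distortion cannot be derived from the article, which gives neither a same-day effect nor a fixed interval from dose to scan. It is zero if no arm-specific same-day effect exists. It should be corrected, because the sub-study as designed cannot support the chronic-only interpretation it announces.

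**What to change.** If follow-up scanning has not begun, have participants take that day's sachet after the scan, matching the rule for pre-dose assessments at the main visits. The cost is one sachet moved away from breakfast on one day, with no extra scans. Flag in the analysis any scan already acquired after dosing.

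If follow-up scanning has begun, keep post-dose scanning, because a switch would mix dosing states among only 20 per arm. Restate the sub-study objective and its conclusions as the on-treatment (acute plus chronic) effect. Then use the 180-day pre- and post-dose middle cerebral artery velocity and computerized test data, already planned, to judge whether an arm-specific same-day effect is plausible. The cost is a change of wording and a supporting analysis of data already being collected.
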